## Abstract

Reproductive genetic carrier screening (RGCS) provides people with information about their chance of having children with autosomal recessive or X-linked genetic conditions, enabling informed reproductive decision-making. RGCS is recommended to be offered to all couples during preconception or in early pregnancy. However, cost and a lack of awareness may prevent access. To address this, the Australian Government funded Mackenzie’s Mission—the Australian Reproductive Genetic Carrier Screening Project. Mackenzie’s Mission aims to assess the acceptability and feasibility of an easily accessible RGCS program, provided free of charge to the participant. In study Phase 1, implementation needs were mapped, and key study elements were developed. In Phase 2, RGCS is being offered by healthcare providers educated by the study team. Reproductive couples who provide consent are screened for over 1200 genes associated with >750 serious, childhood-onset genetic conditions. Those with an increased chance result are provided comprehensive genetic counseling support. Reproductive couples, recruiting healthcare providers, and study team members are also invited to complete surveys and/or interviews. In Phase 3, a mixed-methods analysis will be undertaken to assess the program outcomes, psychosocial implications and implementation considerations alongside an ongoing bioethical analysis and a health economic evaluation. Findings will inform the implementation of an ethically robust RGCS program.

## 1. Background

Reproductive genetic carrier screening (RGCS) is a form of genetic testing that provides prospective parents with information about their chance of having children with severe autosomal recessive and X-linked genetic conditions, thus promoting choice and reproductive autonomy [1,2]. While individually rare, it is estimated that 1–2% of reproductive couples have an increased chance of having children impacted by such conditions [3,4]. Such couples (henceforth referred to as ‘increased chance couples’) may choose to access reproductive options either to avoid, or to plan and prepare for the birth of children with the condition in accordance with their values [5]. These options include prenatal diagnosis (PND), in vitro fertilization (IVF) with preimplantation genetic testing for monogenic disorders (PGT-M), using donor gametes, adoption/fostering or not having children. 

Families can comprise a broad range of structures, and parents may or may not have genetic links with their child (for example, if gamete or embryo donors are used). With respect to RGCS, there are two ‘genetic parents’ (of male and female sex) for the prospective or current pregnancy who can be considered the ‘reproductive couple’. It is important to acknowledge non-genetic parents who may also be involved in the RGCS process with respect to pre-test deliberation and reproductive decision-making. Thus, when referring to ‘couples’ engaging in RGCS, we refer to the collective group who will use the information gained from RGCS to inform future reproductive choices. 

In the past, RGCS was primarily offered to those from certain ethnic backgrounds with a high disease prevalence. However, the recessive nature of these conditions, barriers in family communication of genetic information, and delayed or underdiagnosis of genetic conditions mean most affected children are born to parents who have no known prior history of the condition [6]. Additionally, as populations become increasingly multiethnic, relying on ethnicity ceases to be an effective way to guide offers of RGCS [7,8]. Numerous peak bodies now recognize RGCS as relevant to all people planning a pregnancy or in early pregnancy regardless of family history or ethnicity [9,10,11].

Research demonstrates there is interest in and support for RGCS, provided it is optional and those offered screening are given sufficient time and information to consider their decision [9,12,13,14,15]. Research has shown increased chance couples may initially express shock and anxiety [16], however, over time report feeling empowered by the information and the ability to make value-congruent reproductive choices [17,18]. These findings highlight the importance of providing RGCS within a model that incorporates informed decision-making with high-quality pre-test information and the provision of appropriate genetic counseling support [18,19].

Internationally, there is substantial variation in access to RGCS, as well as differences in the number and type of conditions screened, how results are returned and managed, if the reproductive couple is screened sequentially or simultaneously, and whether government-funded RGCS is available [1,2]. In Australia, RGCS is currently available largely on a user-pays basis, through commercial entities. However, the Australian Federal Government’s Department of Health recently announced a plan for government-funded carrier screening for three conditions (cystic fibrosis, spinal muscular atrophy and fragile X syndrome) to be implemented in late 2023. 

RGCS is usually ordered through healthcare providers, such as general practitioners, obstetricians, midwives, fertility specialists and genetic health professionals. Barriers to RGCS, including test costs and a lack of awareness amongst healthcare providers and the general community, mean that most increased chance couples are not given the opportunity to learn this information prior to the birth of an affected child [20]. Currently, most people who access RGCS do so in early pregnancy, despite this information being most useful prior to conception [20]. Those accessing RGCS also tend to live in metropolitan areas and utilize private healthcare [20,21,22]. Given this inequality in access, a population-based screening approach would enable RGCS to be made more widely available. 

## 2. Methods

### 2.1. Funding and Ethics Committee Approval

This study was funded by the Australian Government’s Medical Research Future Fund as part of the Genomics Health Futures Mission. Human Research Ethics Committee (HREC) approval was obtained to conduct the study in all Australian states and territories (see Supplementary File S1 for a list of HREC approvals). Site-specific governance approval was obtained for recruitment through 22 publicly funded healthcare services (hospitals and clinical genetics services). Site-specific governance approval was not required for recruitment in private healthcare settings (general practice, private obstetrics, midwifery and ultrasound, and some fertility services) as HREC approval was deemed to be sufficient. In addition to the incidental recruitment of Aboriginal and Torres Strait Islander participants, specific HREC approval was obtained to purposefully recruit in Indigenous healthcare settings. 

### 2.2. Aims

The primary aim of MM is to develop and implement a free, easily accessible RGCS program, and assess its feasibility and acceptability. Objectives include: to assess program outcomes, including, the offer and uptake of RGCS, frequency of increased chance couples, and their reproductive decisions and outcomes;to understand the screening experience by measuring psychosocial impacts, including anxiety, factors influencing decision-making, decisional conflict and regret;to evaluate the implementation of RGCS by identifying possible barriers and enablers for key stakeholders, including people offered screening, healthcare providers (HCPs), and clinical and laboratory services delivering RGCS;to assess the health economic implications of RGCS;to understand the bioethical aspects of RGCS and explore the ethical issues arising during the implementation and evaluation of the program.

### 2.3. Study Governance

The MM governance structure is summarized in Figure 1. The study is administered by Australian Genomics [25], a national research network that has a charter to build evidence for the integration of genomic medicine into the healthcare system. 

MM has a National Steering Committee and an International Advisory Group who advise on the strategic direction, research activities and implementation of the study. An Indigenous Advisory Group was convened to advise on the development of a culturally appropriate recruitment approach and materials for Aboriginal and Torres Strait Islander participants. The study also has input from the Australian Genomics Community Advisory Group and established its own Community Reference Group, who have provided input into the design and language of the participant materials and advised on accessibility. 

Six project committees were established to oversee key aspects of the study: Gene Selection, Laboratory, Variant Review, Education and Engagement, Research, and Recruitment and Clinical. The membership of these committees includes representatives from all Australian states and territories, professional bodies including the Royal Australian and New Zealand College of Obstetricians and Gynaecologists (RANZCOG), Royal Australian College of General Practitioners (RACGP), Human Genetics Society of Australasia (HGSA), and Royal College of Pathologists of Australasia (RCPA), as well as professionals involved in the delivery of RGCS. 

The MM study team comprises an Executive Team (the Study Leads, Program Coordinator and Managing Director of Australian Genomics) and an Operations Team (medical scientists, genetic counselors, clinical geneticists, researchers and administrative staff). 

### 2.4. Study Design

The MM study design is outlined in Figure 2. The study commenced in 2019 with an initial plan to recruit 10,000 couples and a completion date of December 2021. However, the SARS-CoV-2 pandemic impacted recruitment and laboratory testing. Thus, the study was extended with a revised recruitment target of 8350 couples and a completion date of December 2022. A longer-term follow-up of the reproductive outcomes will be undertaken in subsequent years. 

The study comprises three phases: (**1) Pre-implementation**, which involved study design and development (2019); (**2) Implementation**, which comprises the two stages of (*2a) Piloting and early implementation* (2020), and (*2b) Nation-wide implementation* (2021–2022); and (**3) Post-implementation**, assessing outcomes (2022 and beyond). The recruitment of couples was designed to occur in a staged manner, with the rate of recruitment increasing progressively over the course of the study. In Phase 2a, screening was offered in four states/territories: the Australian Capital Territory (ACT), New South Wales (NSW), Victoria (VIC) and Western Australia (WA). In Phase 2b, screening was extended to all Australian states and territories, including the Northern Territory (NT), Queensland (QLD), South Australia (SA) and Tasmania (TAS).

#### Evaluation of the Mackenzie’s Mission Reproductive Genetic Carrier Screening Program

As MM is a research study, evaluation is embedded throughout. There are four research streams taking an integrated approach to evaluating the program: psychosocial and epidemiology; bioethics; health economics; and implementation science. Within the psychosocial and epidemiology, health economics, and implementation science streams, empirical research is being conducted using a mixed-methods approach. Data sources include HCPs, people offered RGCS through MM, and the MM study team. The health economics analysis includes an assessment of the health economic impacts of RGCS using data from the literature, the MM study, and data provided by clinical and laboratory services. A bioethics critical analysis, exploring the relevant ethical issues and recommendations for how they can be addressed in the future delivery of RGCS, is being undertaken in parallel. This has focused on the ethical aspects of delivering RGCS at the population scale and has included a consideration of issues such as gene selection and reporting, ethical frameworks, eugenics, and condition severity [5,26,27,28,29,30]. Bioethical perspectives and analysis have been integrated into the consideration of ethical issues that arise throughout MM, and ethical dilemmas encountered while implementing MM have informed the focus of conceptual bioethics research. Collectively, the outcomes from each research stream will inform the development and future implementation of RGCS in Australia. 

**Figure 2 jpm-12-01781-f002:**
[figure not shown]
Mackenzie’s Mission’s study design showing the implementation phases.

^a^ The processes were piloted in four states/territories (Phase 2a) before national implementation (Phase 2b).

### 2.5. Phase 1—Pre-Implementation: Study Design and Development

Figure 2 summarizes the key stages of study Phase 1. During this stage, the Indigenous and Community Reference groups were established, and began to have input into the study design and development. 

#### 2.5.1. Mapping Implementation Needs

To explore the initial HCP knowledge and perspectives on RGCS, and to identify the potential barriers and facilitators to offering RGCS to people in usual care, an HCP survey was developed (HCP survey 1) [31]. This survey used the validated Patient Safety Behaviour Survey [32] informed by the Theoretical Domains Framework, a behavior change framework comprising a compilation of both psychological and organizational theories, which influence behavior and behavioral change [33]. HCPs who may offer RGCS to people seen in their usual practice were approached opportunistically at relevant conference presentations, education seminars and professional meetings, and asked to complete the survey. 

Discussions were undertaken with clinical, laboratory and administrative staff experienced in genetic testing and screening service delivery to understand the elements required to be incorporated into the RGCS program design. Particular attention was focused on ensuring the appropriate resources and supports were in place for increased chance couples, as access can vary by geographical location and healthcare setting across Australia. Physicians specializing in conditions/groups of conditions were engaged and informed about the study in recognition that they may need to be called upon to provide increased chance couples with further information on the condition. 

#### 2.5.2. Developing the Recruitment Approach

To aid this research, an electronic study database was created and housed in the Research Electronic Data Capture (REDCap) platform hosted at the Murdoch Children’s Research Institute [34,35]. To plan for a future, widely accessible RGCS program, it was essential to capture the experience of delivering the screening in a variety of settings. In Australia, healthcare is multifaceted and provided through services that are funded publicly and/or privately; thus, recruitment needed to represent all avenues through which people currently access pre- and early pregnancy healthcare in Australia. General practice, obstetrics, midwifery, ultrasound, fertility and genetics services were identified as potential healthcare settings in which recruitment could occur. Multiple strategies were used to identify recruiting clinics and HCPs (referred to as rHCPs hereafter), including through: existing networks established through their involvement in delivering RGCS or prenatal screening services; Primary Healthcare Networks (groups of independent Australian Government-funded organizations that coordinate primary healthcare in their region); practitioner education events; online searches of practitioners in particular geographic areas; posts on selected relevant social media groups; presentations at conferences; professional networks; word of mouth; and snowball sampling by rHCPs. It was considered essential to recruit as representative of a sample of the Australian population as possible to ensure wide generalizability of the research outcomes from the study. Recruitment targets were set to ensure the representation of people in a variety of geographic areas across Australia using 2016 birth rates in defined geographic regions [36]. Recruitment targets also incorporated the proportion of people accessing public and private healthcare in each region [37]. 

Previous studies show that HCPs who currently provide pre- and early pregnancy care are ideally placed to introduce the notion of RGCS, but that time, a lack of knowledge about RGCS, and competing priorities are barriers to them offering RGCS [38,39]. To address these challenges, an online portal was developed for participant enrollment, education and consent, thereby reducing the requirements of rHCPs to provide detailed information about RGCS. Eligibility criteria were designed to be deliberately broad to enable a wide range of people to take part (Table 1). An effort has been directed to ensure that the study is accessible to people from a broad spectrum of ethnicities, including Aboriginal and Torres Strait Islander people, people with limited English, those without computer/Internet access and those with disabilities. People who already know that they have an increased chance of having children with a serious genetic condition (due to family history and/or previous genetic testing) are included in the study so they can access RGCS for other conditions. 

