#### 2.6.1. Healthcare Provider Recruitment

Contact was made with HCPs and information about the study was provided either in person or via letter, telephone, fax and/or email. For interested HCPs, a link to the HCP survey 2 was sent via email and education was provided through either: a presentation by a study genetic counselor in person or via video conference, a recorded presentation, or an online education module. Some of these rHCPs participated in a trial of education approaches undertaken by the study implementation science team which will be described and reported separately. rHCPs were provided with their own batch of hard copy and/or electronic study invitation/test request forms, each with a unique access code for the participant portal linked to them. Once the rHCP had completed the education module and received their forms, they were able to start recruiting participants.

Recruitment rates for each rHCP have been closely monitored for the purpose of evaluating the geographic reach of the study and to ensure the representativeness of the sample. Where targets have been achieved for geographic regions, recruitment has ceased in that region or rHCPs have been restricted to recruiting patients from certain postcodes. Regular email newsletters/bulletins are sent to rHCPs summarizing study progress and key updates.

During Phase 2, the implementation science research team and Operations team co-designed and implemented several strategies to support rHCPs to offer RGCS, including a video demonstrating how to offer RGCS, posters for waiting and clinic rooms, regular contact with the MM study team, and an evaluation of different education strategies. Data from the HCP survey 2 and study genetic counselor experiences were then synthesized to generate modified implementation strategies that were later trialed (to be reported separately).

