##### Quantitative Analysis

Quantitative data will be analyzed using the statistical software packages, STATA 16 and SPSS. Descriptive statistics will be used to summarize the program outcomes including the RGCS uptake, frequency of increased chance couples and reproductive decisions made by these couples. Detailed participant characteristics will be reported, with the representativeness of the participant sample compared to Australian population data assessed using a minimum dataset (e.g., socioeconomic status via the Index of Relative Advantage and Disadvantage quintile).

Data will be summarized using descriptive statistics (e.g., means, standard deviations, medians, interquartile ranges, frequency distributions and 95% confidence intervals). Inferential analysis will include univariable analysis such as χ^2^ and Fisher exact tests, unadjusted logistic regressions for categorical outcomes, and independent, two-tailed *t*-tests or non-parametric Mann–Whitney U tests for continuous outcomes. A comparison between participants who had RGCS and participants who did not proceed with RGCS after initiating enrollment will be performed using multivariable logistic regression, adjusting for significant covariates (*p* < 0.1 in the univariable analysis).

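### Region and public/private share set the recruitment targets but are not carried into the written analysis of uptake and increased-chance frequency; report both outcomes standardized to those margins beside the crude figures

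*Protocol article*

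**What the plan says.** Section 2.5.2 states the goal: "It was considered essential to recruit as representative of a sample of the Australian population as possible to ensure wide generalizability". It names two control variables. The first is geography: "Recruitment targets were set to ensure the representation of people in a variety of geographic areas across Australia using 2016 birth rates". The second is sector: "Recruitment targets also incorporated the proportion of people accessing public and private healthcare in each region".

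Section 2.6.1 describes the control during recruitment. Each recruiting provider's rate is monitored, and "Where targets have been achieved for geographic regions, recruitment has ceased in that region", or providers are limited to certain postcodes.

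Section 2.7.1, Quantitative Analysis, gives the analysis: "Descriptive statistics will be used to summarize the program outcomes including the RGCS uptake, frequency of increased chance couples" and the couples' reproductive decisions. The summaries listed include 95% confidence intervals. Participant characteristics are to be reported, "with the representativeness of the participant sample compared to Australian population data assessed using a minimum dataset". Region and public/private share are not named there, and no step follows from the comparison.

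The only weights in the article are under Psychosocial Outcomes, where inverse probability weights deal with survey non-response.

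The results have two uses. The Health Economic Analysis bases decision-tree probabilities on study outcomes, and section 2.7 says the results inform an application for national public funding.

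**The concern.** The study chose region and sector as the axes on which the sample should match the country. If the achieved sample misses the targets on either axis, and uptake or increased-chance frequency differs along it, a crude proportion estimates the rate for the achieved mix and not for the national one. The planned comparison would reveal the mismatch on whatever variables it covers, but as written it would not correct it. A confidence interval around the crude figure reflects sampling error only.

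The control during recruitment is partial. Closing a filled region caps over-recruitment and pushes later recruitment elsewhere, but it does not ensure that an under-filled region reaches its target before recruitment ends. The closure rule is geographic, and nothing equivalent is stated for public/private share. The Background notes that people who currently access carrier screening tend to live in metropolitan areas and use private care, so these two axes are sensible ones to check.

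Any distortion would pass into the decision tree and the funding case, both of which concern a national program.

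**Working it through.** The article gives no precision calculation, target shares, achieved shares or stratum-specific rates, so there is no stated figure to reproduce. What follows shows the possible size under assumptions.

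**Inputs from the article**
- N = 8350 couples (2.4). It stands in for both denominators, because the numbers who begin enrollment and who are screened are not given.
- Expected increased-chance frequency of 1–2% (Background).

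**Assumed inputs:** all stratum shares and stratum rates below.

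**Formulas**
- 95% half-width = 1.96 × √(p(1−p)/N)
- Crude minus standardized, two strata = (sample share − target share) × (rate in A − rate in B)
- Design effect = Σ (target share)² / sample share

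**Sampling error**
- Frequency 1%: 1.96 × √(0.01 × 0.99/8350) = 0.21 points (about 84 couples)
- Frequency 2%: 1.96 × √(0.02 × 0.98/8350) = 0.30 points (167 couples)
- Uptake 60%: 1.96 × √(0.6 × 0.4/8350) = 1.05 points

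**Illustrations**

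| Outcome | Stratum A: target → sample share | Rate A / B | Crude | Standardized | Difference (points) | Half-width (points) |
|---|---|---|---|---|---|---|
| Uptake | 30% → 15% | 40% / 60% | 57% | 54% | 3.0 | about 1.05 |
| Uptake | 30% → 15% | 50% / 60% | 58.5% | 57% | 1.5 | about 1.05 |
| Uptake | 70% → 55% | 60% / 80% | 69% | 66% | 3.0 | 0.99 |
| Frequency | 30% → 15% | 1% / 2% | 1.85% | 1.70% | 0.15 | 0.29 |
| Frequency | 30% → 15% | 2% / 1% | 1.15% | 1.30% | −0.15 | 0.23 |
| Frequency | 20% → 10% | 3% / 1.3% | 1.47% | 1.64% | −0.17 | 0.26 |
| Frequency | 20% → 10% | 4% / 1.2% | 1.48% | 1.76% | −0.28 | 0.26 |

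For example, row 1: 0.15 × 0.40 + 0.85 × 0.60 = 0.57, against 0.30 × 0.40 + 0.70 × 0.60 = 0.54. Last row: 0.10 × 0.04 + 0.90 × 0.012 = 0.0148, against 0.20 × 0.04 + 0.80 × 0.012 = 0.0176.

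The difference is zero in every row if the sample share equals the target share or the two rates are equal.

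**Effect on interval coverage.** A shift smaller than the half-width still matters. For 1.85% against 1.70%, the standard error is 0.147 points, so the shift is 0.15/0.147 = 1.02 standard errors and a nominal 95% interval covers about 83% of the time. For 1.15% against 1.30%, the standard error is 0.117, the shift is 1.29 standard errors, and coverage is about 75%.

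**Price of weighting**
- 20% → 10%: 0.04/0.10 + 0.64/0.90 = 1.11
- 70% → 55%: 0.49/0.55 + 0.09/0.45 = 1.09
- 30% → 15%: 0.09/0.15 + 0.49/0.85 = 1.18

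Half-widths therefore grow by about 4–9% (square roots 1.04 to 1.09).

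**The case against.** **Unweighted is an inference.** A reader might conclude that the plan commits to pooled, unweighted national figures. The article says neither word. It says descriptive statistics, and a full protocol or analysis plan that is not shown may add standardization or reporting by region. This stands. What remains is that the article writes out its analysis, names weights where it plans them (survey non-response), and attaches none to these outcomes or to the representativeness comparison.

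**Recruitment was steered.** Postcode restrictions and closed regions move later recruitment toward unfilled areas, and 2.5.2 describes searching for practitioners in particular areas. This stands too: geographic imbalance may be small. It does not show that imbalance is absent, and it does not address sector.

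**Shortfalls are not shown to be likely.** A reader might infer them because "the study was extended with a revised recruitment target of 8350 couples", down from 10,000 (16.5% fewer), or because four states and territories opened only in the second stage. A smaller total changes size and not shares, the study period was extended, and the staged opening was planned. Nor is it evidence of shortfall that "specific HREC approval was obtained to purposefully recruit in Indigenous healthcare settings": that effort was meant to improve representation.

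**Frequency is less exposed than uptake.** The shift exceeds the half-width only in the most extreme row, with 4% in one stratum against 1.2% elsewhere. Nothing in the article points to a difference that large by region or sector. This stands.

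**Births against population.** A reader might see a mismatch between birth-based targets and a comparison with Australian population data. That phrase does not exclude data on births or parents, so no contradiction is shown.

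**Conclusion.** The point holds in limited form. The two variables used to make the sample nationally representative are not carried into the written analysis of uptake and increased-chance frequency, and the planned comparison leads to no adjustment. Recruitment control reduces geographic imbalance without guaranteeing its removal, and no equivalent control is stated for public/private share.

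The size of any resulting error is unknown. Under the assumed inputs, uptake could shift by up to about 3 points against a half-width of about 1, and increased-chance frequency by about 0.15 to 0.28 points against about 0.2 to 0.3. These figures rest on assumed shares and rates and on 8350 as the denominator. They show what is possible and do not predict a bias. It would go too far to say that the decision tree will use biased inputs: the article says only that its probabilities are based on study outcomes.

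This is a worthwhile improvement, because the results feed an economic model and a national funding application and the remedy uses margins the study already has.

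**What to change.** In 2.7.1, Quantitative Analysis, state the following (or confirm it, if a fuller plan already does):

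1. Report uptake and increased-chance frequency twice: unweighted, and post-stratified to the margins behind the targets, namely births by region and public/private share within region. The standardized estimate is Σ (target share × observed rate) over cells.
2. Define uptake here as uptake among those who began enrollment. Under 2.6.2, people who decline the invitation and do not return the decliner survey have no further involvement, so uptake among everyone offered screening cannot be weighted at participant level.
3. Fix in advance a rule for collapsing sparse cells. If the regions were the eight states and territories (an assumption), two sectors would give 16 cells, with on average only 84/16 ≈ 5 to 167/16 ≈ 10 increased chance couples each.
4. Run the decision tree with the standardized figures, at least as a sensitivity analysis.
5. Leave reproductive decisions unweighted. They rest on about 84 to 167 couples, and weights on so few would be unstable.

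**Cost.** The extra analysis is small, since the margins were needed to set the targets and each portal access code is linked to a recruiting provider. Precision falls modestly: the design effect is 1.09 to 1.18 in the two-stratum examples and could be higher with many cells. Because crude figures stay in the report, nothing is lost.

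**Limit.** Standardizing on region and sector does not correct selection through provider networks, snowball recruitment or volunteering. The report should say so.
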